This will be a controlled, randomized, double-masked trial. The Test group will wear the myopia control spectacle lens and the Control group will wear the single vision spectacle lens.

Primary outcome measure:

The mean change from baseline in objective cycloplegic refractive error in each of the groups (Test and Control)

Secondary outcome measure:

The mean change from baseline in axial length in each of the groups (Test and Control)

| Trial Product |
| --- |

Test lenses: Myopia control design spectacle lens, material: 1.6 High-Index plastic.

Control lenses: Single Vision design spectacle lens, material: 1.6 High-Index plastic.

Both test and control lenses will be designed and manufacture by Shamir Optical Industries Ltd.

Both test and control lenses will be mounted on regular frames.

Test lens

The test lens is manufactured in a standard FreeForm technology (exactly like a standard progressive addition lens which is similar in terms of the graduall power profile induced in both lens). It does not demand any special manufacturing processes.

The test lens should be worn exactly like a standard spectacle lens and it should be worn through all day hours. The fitting of the test lens is done exactly like the fitting of the control lens, according to the manufacturer instructions.

Product Labeling and Accountability

The clinical trial coordinator, who is in charge of the randomization procedures, will be also in charge of labeling the test spectacles per each patient prior to sending the spectacles to the site. The investigator will hold a dispensing log in which there will be a documentation of the product:

- on receival from the manufacturer
- on dispensing to the patient
- on receiving back from the patient if applicable

| Enrollment |
| --- |

**136** participants will be enrolled in this trial (including an estimated dropout rate of ~5%), 68 participants will be randomly allocated to the Test group and 68 participants will be randomly allocated to the Control group.

Sample size calculation

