The annual myopia progression rate (in objective refraction) in children in Israel is estimated as 0.6D. The effect estimated is 30% which is a change of 0.18D between the annual myopia progression rate at the test group and the control group. Taking into account a standard deviation of the progression rate of 0.35D (as reported in the scientific literature in western countries), the sample size of each group (test and control) should include 60 children.

Taking into account a drop out rate of 5% and also a certain amount of drop outs during the trial due to high annual myopia progression (as mentioned in the section about terminating the participation in the trial) for which we added 10 more patients, the overall calculated sample size is 136.

Distribution of ages within the sample:

The age range for inclusion in the trial is 6 to 12 years old and the children will be enrolled into two aged groups: young children and older childern. In order to create an equal amount of children within each age group the enrollment will be as follows:

- Young Children: Age ≥6, <9.5: 68 patients
- Older Children: Age ≥9.5, <13: 68 patients

Randomization

Randomization function should be applied separately per each of the two age groups, so that eventually each group will contain an equal number of Test lens wearers and the Control lens wearers.

Randomization function will be applied per each age group by the clinical trial coordinator who will keep the randomization list in a confidential file and will not disclose it to other trial staff members (except for the manufacturing technician at Shamir Optical Industries) until the trial close up unless required in specific cases of trial withdrawals by the investigator.

Inclusion Criteria

- Informed consent form signed and fully comprehended by the parent/legal representative of the child
- Age from 6 to 12 years old
- Both male and female
- Spherical Equivalent refractive error (cycloplegic objective) of -0.50D to -5.00D
- Astigmatism not higher than -1.50D
- Corrected Visual Acuity of not less than 6/7.5 or 20/25
- Willing to wear the trial spectacles for the defined period according the protocol plan

Exclusion Criteria

- Current participation in another clinical trial
- Any general health or ocular health pathology that could affect the treatment
- Allergy or intolerance to cycloplegic eye drops (*name should be stated here*)
- Strabismus
- Amblyopia
- History of ocular injury or ocular surgery

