**Total duration of trial per patient: 24 months.**

**A unique measurement performed using a designated device that measured the refractive error in the peripheral retina and. Duration of measurement – 15 minutes.*

**Axial Length is measured using TOMEY optical biometer OA-2000 (partial coherence interferometry). The measurement is performed without any contact with the patient's eye.

| Ethical Issues |
| --- |

This trial will be conducted according to the applicable local regulations and the GCP. All essential documents will be reviewed and approved by the ethics committee prior to the beginning of the trial. Any amendments of these documents will be reviewed and approved by the ethics committee prior to implantation in the trial.

Informed Consent

The investigator will give the child and their parent/legal guardian a full explanation about the trial and will answer all their question regarding participating in the trial.

The investigator will explain that the child will be able to withdraw from the trial at any stage for any reason.

The child's parent/legal guardian will sign the informed consent form and will receive a signed copy of it.

Data confidentiality

All identification details about the children participating in the trial will be held by the investigator in a secured log file kept at the trial site.

Access to the identification details will not be allowed to any unauthorized party and will not be disclosed in any report/document relating to the trial.

Terminating the participation in the trial

These are the cases in which an early termination of the participation in the trial may occur:

1. Should the myopia progression of the patient will be more than 1.00 D after 1 year or other significant refractive changes (such as more than 0.5[D] cylinder) - the investigator will recommend the patient to discontinue the participation in the trial and to consider using other myopia control treatments such as low dose Atropine drops.
2. Should the far/near VA with the trial spectacles will be less than the best corrected VA of the patient, the investigator will consider recommending the patient to discontinue the participation in the trial.

| Risk Evaluation/Adverse Events |
| --- |

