The optical design of the test lens, with the gradual positive peripheral power, induce a certain amount of aberrations in the peripheral areas of the lens. These aberrations were designed such that a good level of compliance will be achieved so that the children will be able to wear the lens.

Adverse events are unlikely to occur, yet it should be mentioned that a child should not wear this lens in case of one/more of the following exist:

- Feeling significant amount of discomfort while wearing the lens such that the safety of the child might be at risk.
- Vestibular disorders

The children participating in the trial will be free to contact the investigator at any time during the wearing period in order to report any unexpected events that might occur. The investigator will decide based on the report whether the child should be excluded from continuing the trial.

Furthermore, it should be noted that a parallel clinical trial is being conducted these days in AIER hospital in China, managed and supervised by Brien Holden Vision Institution (Australia). The trial is similar to our trial, with the same trial product, on a group of 140 children with the same enrollment criteria, including similar trial procedures and trial plan. The trial started at November 2020, and as for now most of the children has worn the test spectacles for a few months with no adverse events reported.

| Data Management |
| --- |

Database

An electronic data base will be held and maintained, into which all the source data will be electronically transferred from the measuring devices, or if not possible, will be typed in and source data (printouts or location of data) will be kept in the patient's file. At any case, all source data (printouts or location of data) should be kept in the patient's file.

The electronic data base will be backed up on a daily basis

Access to data:

The investigator will be able to allow access to data to the Sponsor (without identification data) as per request.

The investigator will be able to allow access to data to the Monitoring staff according to the monitoring plan that will be defined.

| Data Analysis |
| --- |

Data analysis will be performed by a third party. The trial raw data (without the identification data) will be transferred to the third party following the completion of each follow up visit. The third party will then perform the data analysis and produce a report to the sponsor.

Outcome measures analysis:

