The effect of the test lens compared to the control lens will be evaluated using the outcome measures mentioned above.

Both the primary outcome measure (the mean change from baseline in objective cycloplegic refractive error) and the secondary outcome measure (the mean change from baseline in axial length) will be calculated per each of the follow up periods mentioned above (6, 12, 18 and 24 months).

The objective cycloplegic refractive error will be calculated in Sphere Equivalent units which is: SPH + CYL /2 wherein the SPH and CYL values will be taken from the objective cycloplegic refraction measurement.

The mean change (and its standard deviation) of each of those parameters per each follow up visit will be calculated as the mean parameter at the follow up visit minus the mean parameter at the baseline visit.

The effect of the lens in terms of progression in those outcome measures will be analyzed using t-test (if data normality exists) and also by using linear mixed models which should be adjusted for age, gender, objective refraction (sphere equivalent), axial length, age of myopia onset, parental myopia, daily time wearing spectacles and time spend outdoors.

The effect we expect to have in the test group is a decrease in one/more of those parameters mean change from baseline (decrease in progression from baseline) compared to the control group. Any such finding that will include a p-value≤0.05 will be defined as statistically significant.

This analysis will be performed for all the sample as a whole and also for sub groups of age (younger and older children as mentioned above).

Differences of baseline parameters between the test and control group

The distribution of the following baseline parameters will be calculated per each of the groups, test and control:

- Objective cycloplegic refractive error (Sphere equivalent)
- Axial length
- Age
- Gender
- daily time spent outdoors
- Parental myopia

Should any significant difference be found between the two groups in any of those parameters, an adjustment should be made in the analysis regarding this parameter.

| References |
| --- |

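### The protocol has a third party analyse and report to the sponsor after each follow-up visit, with no pooled interim version, so by-arm results would naturally reach the sponsor before a double-masked 24-month trial ends

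*Protocol*

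**What the plan says.** Three parts of the protocol bear on this.

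- **Masking.** Trial Design states: "This will be a controlled, randomized, double-masked trial".
- **Allocation.** Under Enrollment, Randomization, the list belongs to the clinical trial coordinator, "who will keep the randomization list in a confidential file and will not disclose it to other trial staff members". The manufacturing technician is exempt, and the restriction lasts until the trial closes, apart from specific withdrawal cases. The section mentions neither an outside analyst nor the sponsor.
- **Analysis and reporting.** Under Data Analysis, "The trial raw data (without the identification data) will be transferred to the third party following the completion of each follow up visit". The next sentence reads: "The third party will then perform the data analysis and produce a report to the sponsor". The content follows under the same heading: "The effect of the test lens compared to the control lens will be evaluated using the outcome measures mentioned above". Both outcomes "will be calculated per each of the follow up periods mentioned above (6, 12, 18 and 24 months", by t-test and adjusted linear mixed models, with p≤0.05 called significant.

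Follow-up is 24 months per child. No separate content is described for reports made before that point.

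**The concern.** A trial described as double-masked normally keeps comparative results from interested parties until the data are locked. Here the timing, the recipient and the only defined analysis are all fixed in the protocol, and together they point to by-arm results going to the sponsor while children are still being followed.

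At stake is the conduct of the second half of the trial. Under Terminating the participation in the trial, some of the advice on leaving is discretionary: the first case extends to other significant refractive changes, and in the second the investigator only considers a recommendation. The risk section also leaves continuation to the investigator's judgement after a reported event. If it became known which arm was doing better, that could colour such advice, families' willingness to stay, or the timing of an announcement. No barrier between the sponsor's reports and trial operations is described.

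**Working it through.** The point rests on the text, so the main check sets the sections side by side. One calculation shows how informative an early report could be.

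**1. When and to whom.** Data move after each follow-up visit, and the third party then analyses and reports to the sponsor. Completion of a visit could mean each child's visit or the whole wave. Either way it precedes trial close-up.

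**2. What is analysed.** The only analysis defined is test versus control, at 6, 12, 18 and 24 months. No pooled or masked version is given for earlier reports. Of the four time points, 4 − 1 = 3 (6, 12 and 18 months) come before the end of the 24-month follow-up.

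**3. What the analyst needs.** A two-group t-test or a mixed model with a lens effect needs a group variable. A coded one (A/B) is enough; the named list is not required. The Randomization section provides for releasing neither before close-up. Its exceptions are the technician and specific withdrawals.

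**4. Who the sponsor is.** Trial Product says one company designs and makes both lenses. The background table of expected advantages treats the test lens as the authors' own, under that company's name. That the manufacturer is the sponsor is therefore a reasonable inference, not a statement in the text at hand.

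**5. How informative a 12-month report could be.**

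Inputs, from Sample size calculation: annual difference 0.18 D (30% of 0.6 D), SD 0.35 D, 60 children per group. Power and sidedness are not stated; two-sided 5% and 80% power are assumed.

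- Reproducing the plan's figure: n per group = 2 × (1.960 + 0.842)² × (0.35/0.18)² ≈ 59.4, which rounds up to 60. The t-test version gives 60.3. One-sided 5% with 80% power gives 47, and two-sided 5% with 90% power gives 80, so neither alternative matches.
- Total: 120 × 1.05 + 10 = 136, as stated.
- Power at 60 per group: SE = 0.35 × √(2/60) = 0.0639 D; 0.18/0.0639 = 2.82; 2.82 − 1.96 = 0.86; power ≈ 80.4%.

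The sample size is thus built on a one-year difference. If 0.35 D is the SD of one-year change and the planned 60 per group are available, a by-arm report at 12 months has about an 80% chance of reaching p≤0.05 when the assumed effect is real. That is halfway through follow-up.

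**6. What cannot be computed.** The protocol gives nothing from which to estimate how knowledge of interim results would change retention or termination advice.

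**The case against.** **The by-arm content of interim reports is not stated outright.** The protocol speaks of producing a report, in the singular, and calculating outcomes at each period would also fit one final report tabulating four time points. This stands as a caveat. However, the report is tied to transfers after every visit, and no other content is offered, so by-arm interim reports remain the natural reading.

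**A reader might infer a flat breach of the confidentiality rule.** The documents do not support that. The rule covers the list and other trial staff; an outside analyst is not clearly trial staff, a coded variable would suffice, and group means reveal no child's allocation. The technician's access is a declared exception and adds nothing. What remains is a tension and a gap: the section makes no provision for an analysis that the protocol schedules.

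**A reader might infer that the sponsor would steer withdrawals or lens changes.** The protocol gives it no such role. New lenses follow a fixed refraction trigger, termination advice belongs to the investigator, and reports go to the sponsor, not to sites. The outcomes are objective cycloplegic refraction and non-contact biometry, which limits measurement bias. The remaining exposure is indirect.

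**A reader might add inflation of the false-positive rate from four looks.** That is a separate issue. It comes from calling any finding at p≤0.05 significant, arises equally if all four visits are tested once at the end, and is not cured by delaying reports.

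**A statistical analysis plan, not shown here, may define interim reports.** It may, and silence on such detail would be no finding. But the protocol itself fixes the timing, recipient and analysis, and those need reconciling with its own masking provisions.

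**Conclusion.** The concern holds as a tension within the protocol that should be resolved. Followed as written and read naturally, Data Analysis puts test-versus-control results before the sponsor at up to three time points (6, 12 and 18 months) before 24-month follow-up ends. Trial Design claims double masking, and the Randomization section provides no early release of the list or a code to an analyst.

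This rests on two inferences: that each report contains the comparison defined under the same heading, and that the sponsor is the lens manufacturer. The first is strong but not explicit. The second affects how interested the recipient is, not whether the sections fit together.

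The consequence for retention or discretionary termination advice has no computable size, and objective outcomes keep measurement bias limited. The 12-month power of about 80% shows only that an early by-arm report could be informative; it does not measure bias. The planned sample size is unaffected.

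**What to change.** Amend Data Analysis so that reports before the 24-month data lock are pooled across arms and confined to completeness, data quality and safety. Run between-arm efficacy analyses only after lock and formal unmasking. No new exception in the Randomization section is then needed, because disclosure at close-up is already allowed.

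If a 12-month comparison is wanted, pre-specify it as one analysis after the last child's 12-month visit, state its alpha, and name recipients who are separated from the sites and from lens ordering. For that purpose only, add the analyst holding the group code to the exceptions in the Randomization section.

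The cost is protocol wording and revised reporting instructions for the third party. The drawback is that the sponsor waits longer for by-arm results. How the four visits are tested at 0.05 needs its own resolution.

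### The protocol defines mean change and its SD as a difference of two visit means, which gives no SD of change and, once children drop out, can give a mismatched mean

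*Protocol*

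**What the plan says.** In the protocol, under Data Analysis, Outcome measures analysis, the rule opens with "The mean change (and its standard deviation) of each of those parameters per each follow up visit" and says that these are "calculated as the mean parameter at the follow up visit minus the mean parameter at the baseline visit". It applies to the primary outcome (cycloplegic refraction) and the secondary outcome (axial length) at 6, 12, 18 and 24 months. No other sentence says how change is computed. None says that a change is first formed for each child, or that the baseline mean is limited to children seen at the visit in question.

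The next paragraph says that the effect on progression "will be analyzed using t-test (if data normality exists) and also by using linear mixed models which should be adjusted for age, gender" and further covariates.

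The Sample size calculation rests on a different kind of quantity: "Taking into account a standard deviation of the progression rate of 0.35D (as reported in the scientific literature in western countries". The planned effect is given as "The effect estimated is 30% which is a change of 0.18D between the annual myopia progression rate at the test group and the control group". The same section allows for 5% dropout and adds 10 children for losses due to fast progression. Under Terminating the participation in the trial, progression above 1.00 D after one year leads to a recommendation to leave.

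**The concern.** The rule fails in two ways.

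First, it claims to give an SD. The SD of change depends on how each child's two values go together, and subtracting two group means discards that pairing. The SD of progression used to size the trial keeps it. The written rule therefore cannot produce the quantity on which the design rests.

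Second, a difference of means equals the mean of the differences only when both means cover the same children. The protocol expects children to leave, partly because of their outcome, and the rule does not require matched sets. A baseline mean over all children set against a follow-up mean over attenders would mix true change with a change in the group measured.

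The reported size of both outcomes at every visit is at stake, and so is the t-test if an analyst takes its inputs from this rule.

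**Working it through.** **1. The planned sample size.** Inputs from the Sample size calculation: difference 0.18 D, SD 0.35 D. The significance level of 0.05 is from Data Analysis. Two-sided testing and 80% power are assumed, because neither is stated.

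n per arm = 2 × (1.960 + 0.842)² × 0.35² / 0.18² = 59.4, rounded up to 60. This matches the protocol; power at 60 per arm is 80.4%. The total also reproduces: 60 × 1.05 = 63, and 2 × 63 + 10 = 136. The design thus depends on an SD of 0.35 D for each child's change.

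**2. The SD.** The rule yields none. If someone built one from the two visit SDs as if the visits were independent, it would be √(SD_base² + SD_follow²). The baseline SD is not given, so I assume 0.75 to 1.5 D within the eligible range of -0.50 to -5.00 D, with change independent of baseline, so that SD_follow² = SD_base² + 0.35².

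| Assumed baseline SD (D) | SD as if independent (D) | Power for 0.18 D, 60 per arm |
| --- | --- | --- |
| 0.75 | 1.12 | 14% |
| 1.0 | 1.46 | 10% |
| 1.25 | 1.80 | 8% |
| 1.5 | 2.15 | 7% |

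The table shows what the pairing is worth. The protocol does not prescribe this calculation.

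**3. The mean, with complete or matched data.** The difference of means equals the mean of the differences, so there is no error.

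**4. The mean, with mismatched sets.** The error in one arm is the share lost times the baseline gap between leavers and stayers.

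Share lost: assume normal progression with the protocol's SD of 0.35 D, and means of 0.60 D (control) and 0.60 - 0.18 = 0.42 D (test). The probability of exceeding 1.00 D in a year is then 12.7% in control (z = 0.40/0.35 = 1.14) and 4.9% in test (z = 0.58/0.35 = 1.66). Over 60 children per arm that is 60 × 0.127 + 60 × 0.049, about 10.5, close to the 10 added. Adding 5% general loss gives 17.7% and 9.9%. This supposes that every child above 1.00 D leaves.

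The baseline gap is not given. If leavers start more myopic by the amounts below, each arm's progression is understated as follows:

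| Assumed gap (D) | Control (D) | Test (D) | Between arms (D) | Share of 0.18 D |
| --- | --- | --- | --- | --- |
| 0.25 | 0.04 | 0.02 | 0.02 | 11% |
| 0.5 | 0.09 | 0.05 | 0.04 | 22% |
| 1.0 | 0.18 | 0.10 | 0.08 | 43% |

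With equal loss and equal gaps in both arms, the between-arm shift is zero.

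**5. Simulation.** Two million children per arm, baseline SD 1.0 D, true difference 0.18 D, one change per child. Children above 1.00 D and a random 5% were removed. Averaging each remaining child's own change gives 0.134 D. The difference of visit means gives 0.134, 0.108 and 0.081 D when baseline and change correlate at 0, 0.2 and 0.4.

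**6. Random loss.** Suppose 68 per arm fall to 60 at random and the baseline SD is 1.0 D. The mismatch adds noise of SD 1.0 × √(1/60 - 1/68) = 0.044 D per arm, and √2 × 0.044 = 0.063 D to the between-arm difference. The planned standard error is 0.35 × √(2/60) = 0.064 D, so the added noise is about as large.

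**The case against.** The strongest reply is that the sentence is loose wording for a descriptive summary. A t-test with a normality check needs one value per child. The protocol speaks of an individual patient's progression in its termination rule, the third-party analyst receives raw data, and the mixed model need not use this definition. Which children enter each visit's summary may also be set in an analysis plan that is not shown. Much of this stands, and it is why the harm is conditional. It does not rescue the sentence itself: the protocol states a formula for the SD that cannot be carried out, and that is a wrong rule rather than detail left for later.

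Two stronger readings are tempting:

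- A reader might infer that power falls from 80% to between 7 and 14%. That requires an SD that combines the two visits as if independent, a step found nowhere in the protocol. The planned tests can be run on each child's own change.
- A reader might set a one-arm shift, such as 0.09 D, against the 0.18 D effect and conclude that half of it is lost. Only the difference between the arms' shifts biases the comparison, here 0.04 D.

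Timing also limits the size. Fast progressors are identified after one year, so they would normally be measured at 12 months. Up to then the mismatch comes mainly from the general 5% loss, which largely cancels between arms if the gaps are similar. The unequal loss in step 4 bears mainly on 18 and 24 months. If the effect accrued steadily to 2 × 0.18 = 0.36 D at 24 months, 0.02 to 0.08 D would be about 5 to 22% of it. The simulation removes fast progressors at the same visit at which their change is measured, so it illustrates the mechanism and does not forecast the 12-month result.

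**Conclusion.** The point holds as an error in the stated definition of change for both outcomes. That no SD can come from two means, and that the rule does not match the SD of 0.35 D used for sizing, needs no assumption.

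The error in the mean is conditional. It is absent with complete or matched data, and on average absent if leavers and stayers have the same baseline. With unmatched sets, loss of 17.7% against 9.9% and assumed gaps of 0.25 to 1.0 D, the between-arm difference shifts by about 0.02 to 0.08 D, or 11 to 43% of the annual 0.18 D. Random loss from 68 to 60 per arm adds noise of SD about 0.06 D at an assumed baseline SD of 1.0 D. The documents give neither the baseline SD nor the gap, so these are ranges, not predictions. They do not support a claim that the planned tests lose their power.

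**What to change.** Replace the sentence under Outcome measures analysis with:

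> For each child, change = value at the follow-up visit minus that child's own baseline value. The mean and SD of these individual changes are reported per arm and visit over children measured at both, and the t-test uses these individual changes.

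This costs one sentence. It needs no new data and no change to the sample size, and it brings the analysis into line with the 0.35 D used for sizing. It does not cure the separate bias from the departure of fast progressors: in the simulation, each child's own change among those remaining still gives 0.134 D against a true 0.18 D. That has to be handled on its own.

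### The whole-sample t-test ignores the two age groups used for randomisation, so it is conservative if progression differs by age; a free improvement, minor in size

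*Protocol*

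**What the plan says.** In the Enrollment section, the Protocol sets two equal age groups: "Young Children: Age ≥6, <9.5: 68 patients" and "Older Children: Age ≥9.5, <13: 68 patients". Under Randomization it adds: "Randomization function should be applied separately per each of the two age groups", with the stated aim of equal numbers of Test and Control wearers in each. Overall, "68 participants will be randomly allocated to the Test group and 68 participants will be randomly allocated to the Control group", which means 34 per arm in each age group.

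Under Data Analysis, Outcome measures analysis, the lens effect on the primary outcome (change in cycloplegic spherical equivalent) and on the secondary outcome (change in axial length) "will be analyzed using t-test (if data normality exists"). The same sentence adds linear mixed models adjusted for age and seven other covariates. "This analysis will be performed for all the sample as a whole", and it is repeated within each age group. Neither method is named as decisive, and a result at p≤0.05 on one or more of the outcomes is to be called statistically significant.

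**The concern.** Balanced randomisation within age groups makes any age-group difference in progression cancel out of the Test-minus-Control comparison. An unadjusted two-sample t-test does not use this. It leaves the between-age-group variance in the pooled SD, and so reports a standard error larger than the true sampling error of the difference. The interval is then wider than it need be and the test rejects less often than its nominal 5% when there is no effect.

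The t-test is a planned whole-sample analysis, and its p-value can support a claim by itself. At stake is some power to detect the lens effect, and an interval of the right width for the simplest comparison in the trial.

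**Working it through.** **Inputs from the Protocol (Sample size calculation; Data Analysis).** Progression: "The annual myopia progression rate (in objective refraction) in children in Israel is estimated as 0.6D". Planned reduction: 30%, that is 0.6 × 0.30 = 0.18 D/year. SD 0.35 D, given as one overall value; 60 children per group before dropout; significance at 0.05. Sidedness and power are not stated.

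**Reproducing the plan's figure.** For an unstratified two-sample comparison, two-sided 5% and 80% power:

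n = 2 × (1.96 + 0.84)² × 0.35² / 0.18² ≈ 59.4, rounded up to 60 per group.

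The total also reproduces: 120 × 1.05 + 10 = 136 (or 120 / 0.95 + 10 = 136.3). The sizing therefore uses the overall SD and claims no gain from stratification.

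**Assumed input.** D is the difference between the age groups in mean annual progression. The Protocol does not give it, so 0 to 0.4 D/year is shown. The upper end is two-thirds of the stated mean rate (0.4 / 0.6).

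**Formulas.** With two equal age groups, balanced arms, and a lens effect that is the same in both:

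- share of variance due to age group: R² = (D²/4) / 0.35²
- within-group SD = √(0.35² − D²/4)
- t-test SE = 0.35 × √(2/60) = 0.0639 D
- age-group-adjusted SE = within-group SD × √(2/60)
- ratio of the two = 1 / √(1 − R²)

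Example at D = 0.3: R² = 0.0225 / 0.1225 = 0.184; within-group SD = √(0.1225 − 0.0225) = 0.316 D; adjusted SE = 0.316 × 0.1826 = 0.0577 D; ratio = 0.0639 / 0.0577 = 1.107.

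Rejection rates come from 20,000 simulated trials per setting, 30 per arm per age group, with a true effect of 0 (type I error) or 0.18 D (power).

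| D (D/year, assumed) | Adjusted SE (D) | t-test SE too large by | Type I error, t-test / adjusted | Power, t-test / adjusted |
|---|---|---|---|---|
| 0 | 0.0639 | 0% | 4.9% / 4.9% | 80.4% / 80.4% |
| 0.1 | 0.0632 | 1% | 5.0% / 5.2% | 79.7% / 80.3% |
| 0.2 | 0.0612 | 4% | 4.1% / 5.0% | 81.1% / 83.3% |
| 0.3 | 0.0577 | 11% | 3.1% / 5.0% | 82.0% / 87.2% |
| 0.4 | 0.0524 | 22% | 1.6% / 5.0% | 84.3% / 92.3% |

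The simulation error is about 0.15 points for type I error (√(0.05 × 0.95 / 20,000)) and 0.3 points for power (√(0.8 × 0.2 / 20,000)). The 79.7% is therefore not distinguishable from 80%. The power given up by the t-test is about 0, 1, 2, 5 and 8 points down the table.

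**The case against.** The strongest reply is that the sentence naming the t-test goes on to plan a mixed model adjusted for age. The randomisation groups are defined by age alone, so a continuous age term normally captures most of their effect, and that model recovers most of the precision. Separate analyses within each age group are planned too. This stands: a reader might infer that the benefit of stratifying is lost to the trial as a whole, and the Protocol does not support that. Nor is age instead of age group in the mixed model a defect; adding the two-level factor there would be a preference.

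The size is also conditional. The Protocol gives one progression rate and one SD, with nothing by age group. It presents stratification as a way of getting equal numbers and states no precision aim. A SAP, not shown here, may specify a stratified analysis. All this limits the weight of the point.

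It does not remove the point entirely. The t-test is written into the Protocol as a whole-sample analysis whose p-value counts. The mixed model is not a full substitute for a simple comparison adjusted only for the randomisation factor: it also adjusts for daily spectacle-wearing time, which is not among the baseline items listed for the screening visit. If this means time in the trial spectacles, it is measured after randomisation and could depend on the lens. The rule that adjusts for baseline variables found to differ between arms will rarely bring age in, because stratification makes such a difference unlikely. The within-group analyses each use half the sample, and no combined stratified estimate is described.

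**Conclusion.** The point holds in a limited form, as an optional to minor improvement. If progression differs by age group, the whole-sample t-test is conservative, with a standard error about 1% to 22% too large for assumed differences of 0.1 to 0.4 D/year. If there is no difference, nothing is lost.

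A reader might infer that the trial is underpowered or that its error rate is unsafe. Neither follows. The 60 per group was sized on the overall SD, and the t-test keeps about 80% power or more across the range. Its type I error is at or below 5%, so false positives are not inflated. What is forgone is extra power that the design would give at no cost.

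The figures assume that 0.35 D is the SD across both age groups, that arms stay balanced within age groups, that within-group variances are equal, and that the lens effect is the same in both. The direction of the argument also applies to axial length, but the Protocol gives no SD for it, so no size can be stated.

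**What to change.** Replace the whole-sample t-test with a linear model of each child's change from baseline on lens group plus the randomisation age group (<9.5, ≥9.5 years), or keep the t-test only as supportive. Report the adjusted Test-minus-Control difference with its 95% CI for both outcomes. The mixed model's continuous age term can stay as it is.

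The cost is one sentence of analysis text and one degree of freedom. It needs no new data and no additional children.
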